### ***Implications for South Africa of this trial generating new evidence to support or refute pre-existing evidence***

With the growing number of people with HIV related DSN and its impact on social and physical functioning of individuals, it is important do this trial. Cost and availability of drugs is also important to consider. One recent paper estimated that one year of treatment of painful neuropathy in the USA cost \$17,000 per person per year(12). In addition drugs found to be effective in this condition are expensive. For example lamotrogine is currently R16 per day compared to R 0.30 per day for amitriptyline, according to the Chris Hani Hospital formulary of 2006. In addition, gabapentin is not widely available at present, although that may change in the near future as a local generic version has been registered. Amitriptyline is on the WHO and SA EML, and is relatively cheap and widely available in primary health care clinics as well as hospitals.

### ***Clinical issues of importance when considering drug of choice***

Any drug candidate for treatment of DSN should not have interaction with ARV therapy, either documented or theoretical. For example carbamazepine is not recommended for use with ARV therapy because of drug interaction with nucleosides(13). The SA DOH first and second line recommendations or commonly used drugs by people with HIV such as contraceptive pills, fluconazole do not have listed drug interactions with amitriptyline. Other trials have not found that amitriptyline adversely affects viral load or CD4 counts, or any other blood marker for safety. Therefore it is not considered necessary in this trial to measure viral load. The side effects of the drug should be considered. The Schlay trial and the Kiebertz trials noted that amitriptyline was well tolerated at dosages of up to 100mg per day(6;7). This concurs with local experiences. The pill burden, drug formulation and side effects should also be considered and are proposed to be acceptable for amitriptyline. Since people with HIV often experience multiple pains occurring concurrently, a screening tool validated for HIV related DSN will be used and pain treatments will be documented. Primary

outcome measures will not be changes in mood, sleep or quality of life, since these may be attributable to treatments of other pains.

## **Rationale**

### ***Pathophysiology of NPs***

Although a clear separation between peripheral and central neuropathic pain has been established, peripheral nerve damage has been shown to lead to neuroplastic changes in the central nervous system with somatosensory implications.

DSN in HIV are poorly understood but it is agreed that several pathophysiological mechanisms exist. Neuropathy is characterised by pain related phenomena such as allodynia, hyperalgesia, dysaesthesia and paraesthesia. Sensory dysfunction, for example numbness, pins and needles or loss of vibration sense may also be present. Autonomic responses resulting in mottling of skin may also be seen. Pains are often spontaneous, or evoked by non-noxious stimuli, may be persistent and fluctuating or periodic. Incidence and severity is related to viral load(14). Untreated DSN leads to increasing area of pain, allodynia, and hyperesthesia, as well as sensory loss.

## **Product information**

Amitriptyline has antidepressant properties belonging to the tricyclic group. Indicated use is for management of depressive illness, nocturnal enuresis, and pain relief in chronic pain syndromes. It is well absorbed orally, has a half life of between 10 and 50 hours (average 16 hours). It is extensively metabolized in the liver, involving microsomal hepatic enzymes and eliminated over several days, primarily in the urine.

Contraindications are early post-myocardial infarct period and heart block. Use with caution is recommended in patients with: hyperthyroidism, or on thyroxine therapy; arrhythmias; epilepsy; prostatic enlargement; closed angle glaucoma or impaired liver function.

Amitriptyline has no drug interactions with ARV therapy. Drug interactions include those with antihistamines, antipsychotics, anti-cholinergic type anti parkinsonian agents, cimetidine, fluoxetine, paroxetine, steroids, including oral contraceptives and MAOI drugs. It is not to be used in pregnancy.

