### **Exclusion Criteria**

All conditions which are likely to cause confounding will be excluded from the study, together with conditions which are likely to cause drug interactions.

- Severe pain from DSN caused by ARV drugs which warrants a change in regime
- Already taking amitriptyline drug, or has taken the drugs at least three weeks prior
- Limb amputation
- Kaposi sarcoma of the lower limbs
- Current post- herpetic neuralgia or herpes zoster
- Pregnancy or intention to fall pregnant
- TB treatment
- Malignancy not related to HIV
- Major psychiatric disorders including mania or epilepsy
- Clinically significant renal failure
- Diabetic neuropathy
- Clinically significant liver failure or past history as defined by encephalopathy, oedema and jaundice

- Patient in extreme pain or exhausted
- Participating on another trial or study
- MAOI, other tricyclic antidepressants or anti-epileptic drugs
- Recent myocardial infarction, arrhythmias, heart block
- History of urinary retention, urinary hesitancy or closed angle glaucoma

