### ***Baseline procedure***

The following is the procedure for the baseline visit:

1. Detailed information session on the study
2. Time to consider participation and invite questions and clarification
3. If agrees to join study then administer written informed consent. If not or changes mind then thank the participant for their time
4. For those enrolled collection of demographic data(Appendix 3)
5. Collection of clinical data(Appendix 4)
6. Assessment of peripheral neuropathy(Appendix 5);
7. Review eligibility criteria and if still eligible and consenting then randomization will occur
8. Participant will be given arm treatment, pain diary and written and verbal instructions. They will receive an airtime voucher or telephone card for R28 per month for the duration of the study and a telephone number to call should they need to call the study team

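### The liver exclusion stops at failure, although the protocol advises caution in impaired liver function and lets every participant be titrated by telephone to as much as 150 mg

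*Protocol*

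**What the plan says.** Protocol, Product information, names two contraindications (the early period after myocardial infarction, and heart block) and then the cautions: "Use with caution is recommended in patients with: hyperthyroidism, or on thyroxine therapy; arrhythmias; epilepsy; prostatic enlargement; closed angle glaucoma or impaired liver function". The same section says that the drug is metabolised extensively by hepatic enzymes.

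The exclusion list appears twice with the same items, under Gender considerations and under Exclusion Criteria. It is introduced by "All conditions which are likely to cause confounding will be excluded from the study, together with conditions which are likely to cause drug interactions". The bullets that bear on the cautions are:

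- "Clinically significant liver failure or past history as defined by encephalopathy, oedema and jaundice"
- "Recent myocardial infarction, arrhythmias, heart block"
- "Major psychiatric disorders including mania or epilepsy"
- "History of urinary retention, urinary hesitancy or closed angle glaucoma"

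Thyroid disease and thyroxine appear in no criterion.

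Under Baseline procedure, clinical data are collected at step 5. Step 7 reads "Review eligibility criteria and if still eligible and consenting then randomization will occur". Dosing then follows one schedule for everyone, from 25 mg to at most 150 mg, with each step decided in a nurse's telephone call.

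**The concern.** The protocol singles out impaired liver function as a reason for care with a drug that the liver clears. Its eligibility rule then sets the threshold at liver failure. Between the two lie patients with known impairment that a clinician would call significant but who have not reached failure. Under Inclusion and exclusion criteria, anyone who fits the criteria is eligible, and the text shown states no lower dose ceiling, slower step or extra check for these patients.

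The stake is participant safety before and during titration. Because the design is a crossover, every participant who completes it receives amitriptyline in one period, so an eligible patient with impairment is not spared by allocation to placebo. The thyroid group raises a smaller question of the same kind.

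**Working it through.** No sample size, power or error rate is involved. The check sets the caution list against the exclusions, then looks for any other precaution.

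**1. Cautions against exclusions**

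| Caution group (Product information) | Exclusion Criteria | Reach |
|---|---|---|
| Arrhythmias | cardiac bullet | named |
| Epilepsy | psychiatric bullet | named |
| Closed angle glaucoma | urinary and glaucoma bullet | named |
| Prostatic enlargement | urinary retention or hesitancy only | partial |
| Impaired liver function | failure only | partial |
| Hyperthyroidism or thyroxine | none | absent |

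Named 3 + partial 2 + absent 1 = 6. Both contraindications (2 of 2) are excluded.

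**2. Readings of the liver bullet**

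- The three signs are joined by *and* and define both current and past failure. Then all three are needed, and a patient with jaundice or oedema but no encephalopathy is eligible.
- The signs define past history only. Then current failure is left to clinical judgement, and impairment below failure is still eligible.
- The signs are examples, any one of which is enough. Then a patient with known impairment and none of the three is eligible.

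The readings differ in how much they admit, but each leaves impairment short of failure inside the criteria.

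**3. What happens after enrolment**

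One tablet is 25 mg, so six tablets are 6 × 25 = 150 mg. In the first period the follow-up table has calls on days 3, 7, 11 and 13, and the step to six tablets is possible on day 13. The dose table under Guidelines for introducing amitriptyline puts it on day 15. The first scheduled site visit after baseline is day 21, which is 21 − 13 = 8 or 21 − 15 = 6 days after the maximum dose may have been reached. In the second period the new pack is given on day 63, six tablets are possible on day 75, and the next scheduled visit is day 82, which is 82 − 75 = 7 days later. Unscheduled visits are available, but no scheduled face-to-face contact falls between the first dose and the maximum dose. Eligibility review is therefore the natural point to catch a known liver problem.

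**4. Pace of the steps**

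The steps in the first-period follow-up table are 3, 4, 4 and 2 days apart. The protocol quotes half-lives of up to 50 hours for amitriptyline and 90 hours for its active metabolite. By the five-half-lives rule it uses for washout, these give 5 × 50 = 250 hours (about 10 days) and 5 × 90 = 450 hours (18.75 days). At the long end, levels could still be rising when the next step is decided. These figures are not specific to impaired livers. They show only why clearance matters on this schedule.

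**5. Other precautions in the text**

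Screening procedure describes a short eligibility questionnaire, ankle reflexes and vibration sense. Laboratory results are said to be filed, but no test is named. Precautions specific to liver impairment short of failure, or to thyroid disease: none found in the text shown.

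**The case against.** The best case for the protocol has five parts.

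*A caution is not a contraindication.* This stands. A reader might infer that the eligibility list contradicts the product information. It does not: both contraindications are excluded, the list's stated purpose is confounding and drug interactions, and nothing commits the sponsor to turn every caution into an exclusion. Still, the list already includes heart block, glaucoma and urinary retention, so in practice it serves safety too.

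*General safeguards exist.* This also stands. A study doctor and nurse recruit and screen, dosing starts at 25 mg, adverse effects are asked about at the titration calls, symptoms such as sedation, confusion, dizziness and palpitations are tracked, and a doctor assesses side effects, with the dose held or stopped if needed. To say that these patients are unprotected would be wrong. But these measures respond once side effects appear, whereas an eligibility line acts before the first dose.

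*Earlier trials were reassuring.* The protocol reports no significant difference from placebo on liver function tests and good tolerability up to 100 mg daily. It does not say that this was shown in patients with impaired livers, and the present ceiling is 150 mg.

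*The forms and SOPs are not shown.* They might ask about liver or thyroid history. This limits the point to the written criteria and the visible text.

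*Excluding everyone on thyroxine would go beyond the caution.* This is accepted. The product information asks for care, and stable treated disease can be handled by a doctor's review.

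**Conclusion.** The point holds as a cheap safety improvement, centred on the liver bullet. The written rule admits known, clinically significant impairment short of failure to a single titration schedule for a drug that the protocol itself says is cleared by the liver.

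Three stronger inferences are not supported. The protocol does not contradict itself. The size of the risk cannot be stated, because the documents give no prevalence of liver impairment or thyroid disease and no event rate in such patients. No bias in the primary comparison follows, and the target of 124 is untouched. The count of three named, two partial and one absent describes coverage of the caution list. It does not mean that all six groups ought to be excluded.

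The conclusion assumes that the two exclusion lists are the operative criteria and that no form or SOP, none of which is shown, adds a liver or thyroid precaution. If one does, what remains is to bring the eligibility wording into line with it.

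**What to change.** 1. In both copies of the exclusion list, reword the liver bullet to: *Clinically significant liver failure, or past history of it, shown by encephalopathy, oedema or jaundice, or known clinically significant liver impairment.* Changing *and* to *or* removes the reading that needs all three signs. The last clause closes the gap below failure.
2. For known hyperthyroidism or thyroxine therapy, add a review by the study doctor at the existing eligibility step (Baseline procedure, step 7) before randomisation, and exclude only uncontrolled hyperthyroidism.

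Both are checked from the history and the clinic file. Clinical significance stays a clinician's judgement, as it already is in the renal and liver bullets, so the change catches known cases only.

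Cost: a short protocol amendment, a brief doctor's review for the few items concerned, and a slightly smaller eligible pool. No new test or visit is needed, and the dose steps do not change.

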### ***Amitriptyline for HIV related DSN***

The postulated mechanism of action for HIV related DSN is a balanced reuptake inhibition of both serotonin and noradrenalin(15).

Safety, tolerability and side effects and recommended doses: Studies have noted no significant differences between placebo treated groups and amitriptyline in when compared using ECGs or laboratory tests for viral load, CD4 count, liver function(6;16).

Dose regime, other drug trials have shown effect at 10mg- 150mg. Our regime will be titrated to effect in the following manner: 25mg-50mg-75mg-100mg-150mg, then to stop.

Route- oral route with a frequency: once daily at night to mitigate possible side effects of drowsiness and postural hypotension.

## **Methodological issues**

### ***Placebo***

An inactive placebo will be used. It will be identical looking to the active drug and be manufactured according to Good Manufacturers' Practice (GMP guidelines and standard operating procedures). The use of a placebo rather than proven treatment is recommended here because of the lack of known effective and available treatments. There is no treatment standard in South African except amitriptyline, so no choice for a comparator. The European medicines agency has developed guidelines for clinical development of new medicinal products for neuropathy and they include the recommendation that in the light of poor evidence for a comparator to use a placebo controlled trial. Ethical issues in using placebo in pain trials are discussed below. Inactive placebo is used rather than active since in the investigators experience and from the literature, the low dose used (25-75mg), does not seem to cause common or significant side effects that may differentiate active drug from placebo. The placebo effect in pain studies is well documented and its magnitude has been taken into consideration in calculating the sample size.

### ***Cross over design***

A cross over design is proposed for the following reasons: HIV has a complex disease course, and it is acknowledged that there may be many different mechanisms for the DSN so it is desirable if the participant acts as their own control. It is considered that the disease course will not significantly deteriorate in the follow up period of 15 weeks, although the baseline pain intensity will be measured at the start of each treatment intervention. It is anticipated that the follow up period is not too long to see a significant attrition rate. There will be two sub-groups: those stable on ARV with DSN and those not on ARV drugs. Secondly, the disease process is fairly stable over the proposed 14 weeks and the survival times for most participants will be more than proposed trial period.

Washout period: The SAMF 8 cites a plasma  $t_{1/2}$  of 10-50 hours, but also notes that the nortriptyline metabolite is active. The rule of thumb would be 5 half-lives, but in this case, you'd need to track down the metabolite's elimination. (Handbook of Basic Pharmacokinetics including Clinical Applications (6th edition). Ritschel WA and Kearns GL. APHA, Washington, 2004) gives a  $t_{1/2}$  for nortriptyline of 14-90 hours. On that basis, you'd be looking at a wash-out of at least 450 hours, or 18.75 days. Personal correspondence [name]

### ***Measuring pain intensity***

Pain is a subjective experience so self reported pain scores on a visual analogue scale or 11 point Likert numerical rating scale is recommended. A tool (Brief peripheral neuropathy screening tool, BPNS) which has been validated for screening for HIV related DSN will be used(17) along with another tool the DN4 which is validated for DSN. Electrophysiological variables and sensory evaluation do not correlate with the severity of DSN, so will not be used as measures of primary efficacy. The baseline pain score and subsequent scores will be measures using the 11 point Likert numerical rating scale, plus the DN4 and the BPNS tool.

## **Population**

### ***ARV and no ARV***

The possibility of effect for subpopulations will be factored into the trial design, with a sample size calculated to stratify into two groups, those stable on ARV and those not on ARV drugs. Changes in ARV regime may interfere with DSN, so become confounding factors and difficult to interpret. Thus only those stable on ARV drugs for three or more months will be considered eligible.

### ***Moderate to severe pain***

The European Medical Agency recommends that research is conducted on participants with severe or moderate neuropathic pain only (11).

### ***Genetic consideration***

Work in Australia and at Wits University has indicated that genetic factor may be a significant factor in the development of ARV related ATN and response to treatments. Clinical trials have included few black African participants with DSN(18;19).

### ***Gender considerations***

Neuroplasticity responses may be different in women, as may the metabolism of drugs(19). In SA more women are infected with HIV, yet studies in DSN have been mainly in men.

All conditions which are likely to cause confounding will be excluded from the study, together with conditions which are likely to cause drug interactions.

- Severe pain from DSN caused by ARV drugs which warrants a change in regime
- Already taking amitriptyline drug, or has taken the drugs at least three weeks prior
- Limb amputation
- Kaposi sarcoma of the lower limbs
- Current post-herpetic neuralgia or herpes zoster
- Pregnancy or intention to fall pregnant
- TB treatment
- Malignancy not related to HIV
- Major psychiatric disorders including mania or epilepsy
- Clinically significant renal failure
- Diabetic neuropathy
- Clinically significant liver failure or past history as defined by encephalopathy, oedema and jaundice
- Patient in extreme pain or exhausted
- Participating on another trial or study
- MAOI, other tricyclic antidepressants or anti-epileptic drugs
- Recent myocardial infarction, arrhythmias, heart block
- History of urinary retention, urinary hesitancy or closed angle glaucoma

## **Hypothesis**

Amitriptyline is superior to placebo in the management of moderate to severe HIV related peripheral neuropathy.

## **Primary outcome measures**

Self reported pain intensity measurement is the primary outcome measure.

## **Secondary outcome measures**

These will be adverse side effects of treatment, minimum efficacious doses, maximal tolerated doses, mood and effect on activities of daily living

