### ***Follow up procedures: Day 4-day 15***

At home: one tablet will be taken at night for three nights. On the third day the study nurse will call to enquire as to adverse effects, pain score and any other problems, and advice on the next dosage. If the pain has abated significantly the dose will be left at one tablet at

night. If not, the dose will be increased to two tablets at night for three nights. The same procedure will occur until a maximum of 6 tablets at night has been reached. The participant will continue to take this dose for 4 weeks. A weekly telephone call will be conducted by the study nurse.

|                         |                                                                                                                                                                                                                                                                                                   |
|-------------------------|---------------------------------------------------------------------------------------------------------------------------------------------------------------------------------------------------------------------------------------------------------------------------------------------------|
| Day 3                   | The study nurse will call to enquire as to adverse effects, pain score and any other problems, and advice on the next dosage. If the pain has abated significantly the dose will be left at one tablet at night. If not, the dose will be increased by two tablets at night for three nights.     |
| Day 7                   | The study nurse will call to enquire as to adverse effects, pain score and any other problems, and advice on the next dosage. If the pain has abated significantly the dose will be left at two tablets at night. If not, the dose will be increased to three tablets at night for three nights.  |
| Day 11                  | The study nurse will call to enquire as to adverse effects, pain score and any other problems, and advice on the next dosage. If the pain has abated significantly the dose will be left at three tablets at night. If not, the dose will be increased to four tablets at night for three nights. |

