### **Guidelines for introducing amitriptyline**

Patients in this group will be given amitriptyline according to the following protocol. The dose of the drug will not be affected by the weight of the patient.

| Dose                                                                 | Days   |
|----------------------------------------------------------------------|--------|
| 25mg od at night
increase the dose on next visit if pain persists | Day 0  |
| 50mg od at night
increase the dose on next visit if pain persist  | Day 3  |
| 75mg od at night
increase the dose on next visit if pain persist  | Day 7  |
| 100mg od at night                                                    | day 11 |
| 150 mg od at night                                                   | Day 15 |

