### **Side effects**

Side effects will be continually monitored throughout the study as part of symptom control. (Appendix IV)

| Amitriptyline |
|----------------------|
| Dry mouth            |
| Sedation             |
| Weight gain          |
| Confusion            |
| Dizziness            |
| Palpitations         |
| Constipation         |

|       |
|-------|
| Other |
|-------|

Patients who develop side effects will be assessed by a doctor. Patients assessed as having serious adverse events will be withdrawn from the study, and reasons recorded. The total period of the study will be 6 weeks from enrolment. After being enrolled, subjects will be monitored for pain relief, symptom control and quality of life by the nurse, after which an intervention will be put in place. Monitoring will be done weekly by a professional nurse. Intervention can be one of the following:

- Increase the dose, and continue with the trial
- Maintain the dose, and continue with the trial
- Stop the drug because of adverse events, and drop from the study

For those that have been found to be not effective, alternative treatment will be offered.

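### The minimum efficacious dose and maximal tolerated dose cannot be validly estimated, as named, under this titration rule

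*Protocol*

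**What the plan says.** The Study Summary and the section Secondary outcome measures both name a lowest effective and a highest tolerated dose. In the latter the words are "minimum efficacious doses, maximal tolerated doses". They are two of five secondary outcomes, beside side effects, mood and daily activities.

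The section Amitriptyline for HIV related DSN describes titration to effect through 25, 50, 75, 100 and 150 mg, where it ends. In Follow up procedures: Day 4-day 15, the nurse telephones every few days and escalation ends on response: "If the pain has abated significantly the dose will be left at one tablet at night", with matching wording at most later steps. The reached dose is then kept for about four weeks. Guidelines for introducing amitriptyline words the rule differently: "increase the dose on next visit if pain persists". Side effects lists three actions: increase, maintain, or "Stop the drug because of adverse events, and drop from the study".

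On kinetics, Product information gives the parent drug a half-life of 10 to 50 hours, average 16. Cross over design gives a half-life "for nortriptyline of 14-90 hours", the active metabolite, and derives the washout from it: "The rule of thumb would be 5 half-lives", hence "you'd be looking at a wash-out of at least 450 hours, or 18.75 days".

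**The concern.** A minimum efficacious dose and a maximal tolerated dose are properties of a drug in a patient. To learn the first, one must know that the response came from the dose being taken and that a lower dose would not have been enough. To learn the second, one must go up until the dose is not tolerated and confirm the level below.

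This titration does neither reliably. It moves on within two to four days, stops when the patient responds, and offers no listed way back down. A figure reported under either name would partly describe the titration rule. A reader could take it as dosing information for a drug that the protocol says is already widely used and recommended in South Africa.

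**Working it through.** **Maximal tolerated dose.** No arithmetic is needed; follow each possible course.

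| Course | What is learned about the tolerated dose |
|---|---|
| Responds at dose d and is held there | at least d (right-censored) |
| Does not respond, reaches 150 mg and stays | at least 150 mg (right-censored) |
| Stops for side effects at a step | between the previous step and this one; the lower dose is not confirmed, because the participant leaves |

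The better the drug works, the more participants fall in the first row. The Data collection, management and analysis section plans an analysis of those who reached the maximum dose. It names side-effect cases and losses to follow-up as excluded, but not the responders held at a lower dose.

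**Minimum efficacious dose: accumulation.** The protocol's own figure reproduces: 5 × 90 h = 450 h, and 450 / 24 = 18.75 days. Five half-lives at the other values are:
- 16 h: 80 h, or 3.3 days
- 50 h: 250 h, or 10.4 days

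The fraction of steady state after a first step of 72 h is 1 − 2^(−72/t½):
- 14 h (low end, metabolite): 97%
- 16 h (average, parent): 1 − 2^(−4.5) = 96%
- 50 h (upper end, parent): 1 − 2^(−1.44) = 63%
- 90 h (upper end, metabolite): 1 − 2^(−0.8) = 43%

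For later steps I assumed a one-compartment linear model that carries over what is already there: level = d + (previous level − d) × 2^(−Δt/t½). With period 1 calls on days 3, 7, 11 and 13, the level at each decision, as a share of steady state on the dose then taken, is:

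| Half-life | Day 3 (25 mg) | Day 7 (50 mg) | Day 11 (75 mg) | Day 13 (100 mg) |
|---|---|---|---|---|
| 16 h | 96% | 99% | 99% | 97% |
| 50 h | 63% | 82% | 88% | 83% |
| 90 h | 43% | 62% | 72% | 68% |

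At 90 h the whole escalation (13 days in the procedures table, 15 in the dose table) is shorter than the 18.75 days needed at a single dose.

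**Minimum efficacious dose: time and placebo response.** A higher step is always a later step. Placebo tablets are titrated by the same rule, so the placebo period also yields a dose at response.

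**The two periods.** Period 1 steps last 3, 4, 4 and 2 days (calls on days 3, 7, 11 and 13). Period 2 starts on day 63 with calls on days 66, 69, 72 and 75, which gives 3 days each. The decision at three tablets therefore falls on day 11 in period 1 and on day 72 − 63 = 9 in period 2. Dose at response is not on one time scale.

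**Wording that does not agree.**
- One text holds the dose if pain has clearly eased; the other raises it if pain is still present. Neither term is defined, and partial relief could meet both.
- Six tablets can start on day 13 in the procedures table, but 150 mg starts on day 15 in the dose table.
- At the first step the text goes up to two tablets, while the day 3 row goes up by two.

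**The case against.** The strongest reply has several parts.

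- **Titrating to effect is the usual way to look for a patient's lowest effective dose.** This stands: stopping on response does not by itself defeat that outcome. The trouble is the confounding with time, placebo response and possibly accumulation.
- **The placebo period is a built-in comparator.** This also stands, for groups. It shows how much of the holding at each step is time and expectation. It does not turn an individual's final dose into a minimum.
- **The four-week hold brings levels to steady state.** Correct: 672 h is about 7.5 half-lives even at 90 h, so more than 99%. End-of-period pain reflects the dose held. Whether a lower dose would have sufficed remains unknown.
- **Definitions may sit in an analysis plan that is not shown.** They may, but no definition can supply doses that participants never took.

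A reader might also infer stronger points that the protocol does not support:

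- *That the steps break an accumulation time set by the protocol.* It states none. The 450 h is a washout figure from the top of the metabolite range, and at the average parent half-life three days are nearly enough.
- *That the minimum dose is biased upward.* Slow accumulation credits a response to a later, higher step, but early placebo response stops titration low. The net direction is open.
- *That dose reduction is forbidden.* It is not listed, which is weaker.
- *That dose-finding is the trial's purpose.* The stated purpose is effectiveness against placebo.

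**Conclusion.** The point holds in this form: the two outcomes cannot be validly estimated as named. To say that nothing can be measured would go too far, since the dose reached and the step at which people stop can both be described.

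The censoring of the tolerated dose is the firmest part. It follows from the text alone and affects all responders and all who reach the cap. The confounding of dose at response with time and placebo response is also structural. The accumulation part depends on the half-life (96% of steady state after the first step at 16 h, 63% at 50 h, 43% at 90 h). For later steps it also depends on the assumed one-compartment model.

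The consequence is confined to two descriptive secondary outcomes. Nothing here touches the primary outcome or the sample size.

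**What to change.** In the Study Summary and in Secondary outcome measures, replace the two outcomes with:

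1. the dose level (number of tablets) reached at the end of titration, tabulated by treatment and period, with the placebo period as comparator;
2. the proportion of participants stopping for side effects at each dose step, by treatment.

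Add a sentence that neither estimates a minimum effective or a maximum tolerated dose, and that the tolerated dose is censored by response and by the cap.

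The cost is small. The nurse already asks about side effects and advises on dose at each call. The protocol does not list the number of tablets taken among the items asked, so check that the forms record it, together with the step at which anyone stops. The price is giving up a dose claim that the design cannot support.

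Separately, three inconsistencies must be reconciled by those responsible for the clinical rules: the two wordings of when to escalate, day 13 against day 15 for the last step, and up to two against up by two tablets at the first. No dose, step or criterion is proposed here.
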